#### Primary outcomes

Patient-reported functional outcomes

Functional status will be evaluated by means of the DASH questionnaire (validated for the Portuguese language [28]) at the following intervals: 2 weeks PO, 8 weeks PO, 12 weeks PO, 6 months PO, and12 months PO.

Pain

Will be evaluated by means of the VAPS and an algometer [29,30] (the digital algometer used will be a FPIX 50 – Wagner Pain Test Digital Algometer), which is to be applied in the location where pain is reported by the patient, at the following times relative to treatment: 2 weeks PO, 8 weeks PO, 12 weeks PO, 6 months PO, and 12 months PO.

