**Methods/Design:**

The study is randomized clinical trial with parallel groups and a blinded evaluator and involves the surgical interventions EF and VP. Patients will be randomly assigned (assignment ratio 1:1) using sealed opaque envelopes. This trial will include consecutive adult patients with an acute (up to 15 days) displaced, unstable fracture of the distal end of the radius of type A2, A3, C1, C2 or C3 by the Arbeitsgemeinschaft für Osteosynthesefragen–Association for the Study of Internal Fixation classification and type II or type III by the IDEAL^32^ classification, without previous surgical treatments of the wrist. The surgical intervention assigned will be performed by three surgical specialists familiar with the techniques described. Evaluations will be performed at 2, and 8 weeks, 3, 6 and 12 months, with the primary outcomes being measured by the Disabilities of the Arm, Shoulder and Hand (DASH) questionnaire and measurement of pain (Visual Analog Pain Scale and digital algometer). Secondary outcomes will include radiographic parameters, objective functional evaluation (goniometry and dynamometry), and the rate of complications and method failure according to the intention-to-treat principle. Final postoperative evaluations (6 and 12 months) will be performed by independent blinded evaluators. For the Student’s *t*-test, a difference of 10 points in the DASH score, with a 95% confidence interval, a statistical power of 80%, and 20% sampling error results in 36 patients per group.

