#### Surgical techniques

Closed reduction and linear external fixator.

The linear external fixator to be used will be a radiotransparent bar with two pin fastening platforms, with one platform being proximal on the radius and the other platform distal on the second metacarpal, offered by Synthes (code – 03.304.220S). Four threaded self-drilling pins will be used with the proximal platforms that are 4.0 mm in diameter and the distal platforms that are 2.5 mm in diameter. Osteosynthesis with an external fixator will be achieved by the following surgical technique: closed reduction of the fracture by the reduction technique employing traction and contraction manipulation; confirmation of reduction with the image intensifier; a longitudinal incision of 1.5 mm in the dorsal aspect of the forearm and 8 cm proximal from the wrist joint on the longitudinal axis of the radius; exposure of the dorsal cortex of the radius by blunt dissection, introduction of the soft tissue protector positioned at a right angle to the coronal plane of the forearm; introduction of two 4.0 mm self-drilling Schanz pins with a T-handle; double 0.01 cm incisions over the dorsal aspect of the diaphysis of the second metacarpal with a 1 cm spacing between them; dissection and exposure of the dorsal cortex of the metacarpal; placement of the soft tissue protector at a right angle to the coronal plane of the hand; introduction of two 2.5 mm self-drilling Schanz pins, with a technique similar to that for the proximal pins, in the diaphyseal region of the second metacarpal. Should the fracture be intra-articular, this surgical technique may be combined with percutaneous fixation with 1.5 or 2 mm K-wires. Where dorsal comminution is present, a bone graft may be performed with bone removed from the iliac.

Open reduction with volar approach and volar locked plate.

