The volar fixed-angle locking plate offered by Synthes (code −442.493) will be used with unlocked 3.5 cm screws in the cortex proximally and with 2.4 and 2.7 mm locked screws distally. Osteosynthesis with a VP will be achieved by the following surgical technique: volar incision initiated 1 cm distal to the fold of the wrist extending longitudinally in the proximal direction about 8 cm, centered over the radial flexor tendon (RFT); incision of the superficial fascia, freeing the RFT; opening of deep fascia; section of the quadrate pronator muscle 1 cm from its radial insertion with exposure of the fracture; reduction of the fracture and temporary fixation with 1.5 or 2.0 mm K-wires; confirmation with image intensifier; placement of the volar plate; proximal placement of an unlocked screw; confirmation of correct plate plate position by radioscopy; distal placement of two to five locked screws and two additional unlocked screws proximally; layer and skin closure with sutures. Where the fracture is intra-articular this may be combined with percutaneous fixation with 1.5 or 2 mm K-wires. Application of occlusive dressing and palmar forearm splint will be removed on postoperative (PO) day 14.

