### Statistical methods

Epidemiological data will be collected (age, sex, type of fracture, time between fracture, and treatment). Standard deviations or confidence intervals, in the case of percentages, will be provided for each type of data. As a method for confirming randomization effectiveness, data will be compared when stratified by assignment group.

The assumption of normality will be verified by the Shapiro-Wilk test for the use of parametric tests. A Pearson’s chi-square test will be employed to analyze results from the two groups involving categorical variables. A Student’s (parametric) *t*-test will be used for comparing groups of numeric variables. Paired t-tests (parametric) and Wilcoxon tests (non-parametric) will be used to compare clinical progression at intervals of 2-, 8-, and 12-weeks PO and subsequently at 6- and 12-months PO. The significance level used in all statistical tests is to be 5% (alpha = 0.05), with tests having a P value less than 0.05 being statistically significant.

Should differences be found in primary outcomes, then statistical methods will be used to test whether there is robust correlation between epidemiological factors or fracture seriousness and the observed functional outcomes. In addition, we intend to employ Kaplan-Meier survival analysis to evaluate drop-outs should high rates of complications (greater than 20%) occur in either assignment group.

Patients who experience treatment failures and require additional surgery will be monitored and their results computed in the primary assignment group (intention-to-treat principle). Provisions are to be made for blinded statistical analysis of data by a statistician who is unfamiliar with the objectives and outcomes of interest.

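### The algometer, one of two instruments for the primary pain outcome, has its site set by the patient's own pain report, so a pain-free patient has no defined site and other patients' sites can move

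*Protocol article*

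**What the plan says.** The abstract (Methods/Design) lists among the primary outcomes "measurement of pain (Visual Analog Pain Scale and digital algometer". The Background and the Primary outcomes section say the same.

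The Primary outcomes section gives one rule for where the algometer goes: "which is to be applied in the location where pain is reported by the patient". The article names no anatomical landmark and no reference reading. It has no rule for a patient without pain or with more than one painful place.

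In that section the DASH schedule is "2 weeks PO, 8 weeks PO, 12 weeks PO, 6 months PO, and12 months PO", and the same five times are given for pain. Table 2 marks the algometer at all five, with no condition that pain be present.

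Under Statistical methods, a Student's t-"test will be used for comparing groups of numeric variables", and paired t-tests or Wilcoxon tests "will be used to compare clinical progression at intervals of 2-, 8-, and 12-weeks PO and subsequently at 6- and 12-months PO".

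The Surgical techniques section puts the operative sites in different places. The plate arm has a "volar incision initiated 1 cm distal to the fold of the wrist extending longitudinally in the proximal direction about 8 cm". The fixator arm has proximal pins through an incision "in the dorsal aspect of the forearm and 8 cm proximal from the wrist joint on the longitudinal axis of the radius" and distal pins through "incisions over the dorsal aspect of the diaphysis of the second metacarpal".

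**The concern.** A reading that exists for everyone and means the same thing for everyone can be compared by a t-test. This rule secures neither.

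- **Whether there is a site depends on the outcome.** Having pain at 6 or 12 months is a result of treatment and recovery. The patients who do best are the ones for whom the rule gives no place to measure. They are then either missing or measured at a point the assessor improvises.
- **Where the site is depends on the outcome too.** Tenderness over a volar scar, a dorsal forearm pin track or the second metacarpal cannot be assumed to lie on one scale. The sites may follow the operation received, so part of an arm difference could reflect anatomy.
- **Paired comparisons need the same quantity twice.** If the painful place moves, the two readings are of different tissue. If the pain resolves, the second reading has no defined site.

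At stake is the validity of one of the two pain instruments that the article calls primary and would test at the 5% level.

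**Working it through.** The article states no figure for the algometer: no expected value, SD, effect size or share of patients without pain. There is thus no figure of the plan's own to reproduce on this point. The 36 per group was calculated for DASH only, and without a stated SD.

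**Step 1: the rule against the schedule.** Table 2 asks for a reading in every patient at five visits. The site rule supplies a place only if pain is reported. For a pain-free patient both cannot be followed as written. The intention-to-treat statement does not resolve this: it says which group a patient counts in, but supplies no reading.

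**Step 2: what happens to the arm difference if pain-free patients are unmeasured.** This is an illustration; all inputs are assumed. Let the true difference in mean threshold be δ = 0.50. Let h(x) = φ(x)/(1 − Φ(x)), the mean of a standard normal above x.

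*Model A.* Latent pain is normal with SD 1, a patient is in pain if it exceeds 0, and the threshold falls one unit per unit of pain. The unit is the SD of latent pain. The control arm has mean 0 (50% in pain) and the better arm has mean −δ.

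Difference among those in pain = δ − [h(δ) − h(0)].

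- δ = 0.50 (50% v 31% in pain): 0.50 − (1.141 − 0.798) = 0.157.
- δ = 1.00 (50% v 16% in pain): 1.00 − (1.525 − 0.798) = 0.273.

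*Model B.* The threshold has SD 1 and correlates ρ with the variable that decides whether a patient is in pain. The cut-off lies midway between the arms, so about 60% v 40% are pain-free.

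Difference among those in pain = δ − ρ[h(δ/2) − h(−δ/2)] = 0.50 − ρ(0.964 − 0.646) = 0.50 − 0.318ρ.

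| ρ | apparent difference | share of 0.50 lost |
|---|---|---|
| 1.0 | 0.18 | 64% |
| 0.7 | 0.28 | 44% |
| 0.4 | 0.37 | 26% |

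Simulation of Model B gave 0.183, 0.279 and 0.374, in agreement. Taking both models at δ = 0.50, the apparent difference runs from about 0.16 to 0.37. At ρ = 0 the mean would not be biased; only patients would be lost.

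**Step 3: loss of patients alone.** Take 36 measured per group and the standardised difference d that this size detects with 80% power, two-sided 5%: d = (1.96 + 0.842) × √(2/36) = 0.66. With a fraction f unmeasured in each arm, power = Φ(d√(36(1 − f)/2) − 1.96).

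- f = 20%: 71%
- f = 40%: 58%
- f = 60%: 43%

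This d is a benchmark, not an effect claimed for the algometer.

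**Step 4: site.** None of these calculations contains an effect of measuring different tissues. The documents hold nothing from which to size it.

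**The case against.** The strongest reply is that this is an article. Where the probe goes in a patient without pain is procedural detail that a full protocol may hold, and two cited sources stand directly after the algometer is named. A fallback could be in either. That limits what can be said about the missing fallback. It does not dispose of the point, because the article does state a site rule, and that rule makes the site depend on a post-randomisation outcome.

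Several stronger readings are tempting and are not supported:

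- **That pain-free patients drop out.** Table 2 has no such condition and the Statistical methods section has no such exclusion. Dropping them is one possible handling; measuring at an improvised point is another.
- **That the arms are measured at different sites.** The rule allows it and the operative anatomy makes it plausible, but the article does not say it occurs.
- **That about 70% of the effect is lost.** Model A gives 69% and 73%, but Model B gives 26% to 64%. Both rest on assumed values and on all pain-free patients being unmeasured.
- **That the effect is reversed.** In both normal models the sign is kept. An example can be built in which treatment clears only mild pain, so that those left in pain look worse on average, but nothing in the article points to that pattern.

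It is also fair to say that tenderness at a pin track or incision is a real consequence of treatment. A fixed landmark placed clear of both would miss it. That argues for keeping the painful-site reading, not for using it as the compared value.

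Finally, the hypothesis concerns patient-reported function, DASH alone drives the sample size, and the visual analogue scale needs no site. All of that stands, and it confines the damage to one instrument.

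**Conclusion.** The point holds in limited form. The stated rule leaves a primary measure without a defined site in pain-free patients, and lets the site vary by patient, visit and possibly arm in the rest. Neither the t-test nor the paired tests can be read cleanly on such values.

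If pain-free patients go unmeasured, a true difference of 0.50 SD would shrink to roughly 0.16 to 0.37 SD. That range rests on normal distributions, on 31% to 60% of each arm being in pain, and on a correlation between threshold and pain status of 0.4 to 1.0. None of these comes from the article. The direction, attenuation, is better founded than the amount. Conclusions on DASH and on the visual analogue scale are not touched.

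**What to change.** Amend the Pain paragraph and the assessor instructions so that:

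1. At every visit, every patient, in pain or not, has an algometer reading at the same prespecified landmark or landmarks on the operated wrist, identical in both arms.
2. This reading is the value used in the between-arm and paired comparisons.
3. Where pain is reported, a reading at that site is also taken, its location is recorded, and it is reported as a supplementary measure. The instruction should say what to do when there are several painful sites.

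A reading at the same points on the other wrist is optional. The exclusion of bilateral fractures and of previous disorders of either wrist makes that side a usable reference.

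The cost is a change of wording and a few extra minutes per visit with the same device and assessor. A fixed point may miss a patient's worst spot, which is why the painful-site reading is kept. The change needs to be in place before assessments are made, since readings not taken at a common site cannot be recovered in the analysis.

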#### Secondary outcomes

Radiographic parameters

Measurement of angular displacements [26,31,32] and associated lesions [33]. The radial length, radial inclination, volar tilt, ulnar variance, and articular fragment will be measured and considered in the evaluation of radiographs in the posteroanterior and lateral views at the following times relative to treatment: preoperative, 2 weeks PO, 8 weeks PO, 12 weeks PO, 6 months PO, and 12 months PO. Measurements will be performed independently by two researchers on different occasions.

Objective functional evaluation

Arcs of motion will be measured for the wrist and the metacarpal-phalangeal joints of the 1st to the 5th fingers (a goniometer will be employed), palm grip strength (a “Jamar Plus – Hand Dynamometer” digital model dynamometer will be used), pulp-to-pulp, three-point and lateral pinch strength (a digital pinch dynamometer, model “Jamar Digital Pinch Gauge”, will be used), at the following times relative to treatment: 2 weeks PO, 8 weeks PO, 12 weeks PO, 6 months PO, and 12 months PO.

Complications

Any clinical situation will be considered a complication if it requires treatment by a clinical procedure or surgery not provided for in the protocol. All complications will be recorded for subsequent stratification into major and minor complications.

Method failure

Any complication will be considered a method failure if it involves an interruption or change in the treatment method from the method previously randomized.

### Statistical methods

Epidemiological data will be collected (age, sex, type of fracture, time between fracture, and treatment). Standard deviations or confidence intervals, in the case of percentages, will be provided for each type of data. As a method for confirming randomization effectiveness, data will be compared when stratified by assignment group.

The assumption of normality will be verified by the Shapiro-Wilk test for the use of parametric tests. A Pearson’s chi-square test will be employed to analyze results from the two groups involving categorical variables. A Student’s (parametric) *t*-test will be used for comparing groups of numeric variables. Paired t-tests (parametric) and Wilcoxon tests (non-parametric) will be used to compare clinical progression at intervals of 2-, 8-, and 12-weeks PO and subsequently at 6- and 12-months PO. The significance level used in all statistical tests is to be 5% (alpha = 0.05), with tests having a P value less than 0.05 being statistically significant.

Should differences be found in primary outcomes, then statistical methods will be used to test whether there is robust correlation between epidemiological factors or fracture seriousness and the observed functional outcomes. In addition, we intend to employ Kaplan-Meier survival analysis to evaluate drop-outs should high rates of complications (greater than 20%) occur in either assignment group.

Patients who experience treatment failures and require additional surgery will be monitored and their results computed in the primary assignment group (intention-to-treat principle). Provisions are to be made for blinded statistical analysis of data by a statistician who is unfamiliar with the objectives and outcomes of interest.

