### Reducibility criteria

Fractures will be considered displaced if they show, before manipulation, loss of at least one of the criteria below. Fractures will be considered reducible if the radiographic parameters below [16,26] are achieved after manipulation under anesthesia (he contralateral side will be used as a reference):

– Radial length – accepted loss of up to 3 mm

– Radial inclination – accepted loss of up to 8°

– Volar tilt – accepted loss of up to 15°

– Ulnar variance – accepted difference of up to 2 mm

– Articular fragment with displacement – accepted up to 2 mm

Patients in the study will include those presenting a distal radius fracture of the 23A2, 23A3, 23C1, 23C2 or 23C3 types by the AO-ASIF classification and types II and III by the IDEAL classification that are displaced in the initial x-ray and can undergo closed reduction after manipulation under anesthesia.

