### Exclusion criteria

Patients presenting one or more of the following criteria will be excluded from the study:

– Patients with marginal fractures or fractures from a shearing mechanism

– Patients with irreducible fractures

– Patients with prior history of a degenerative or traumatic disorder of the affected or the contralateral wrist joint: identified from the clinical history or diagnosed by x-rays (posteroanterior or lateral view of the wrist).

– Patients with bilateral fracture, fractures exposed to or associated with tendon or neurovascular lesions

– Patient with systemic diseases or traumatic lesions associated with the facture that restrict the application of methods or the evaluation of results

– Patient with a cognitive deficit that does not allow the patient to understand the elements of the functional evaluation

– Consent Form Refusal

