### Surgical intervention

#### Initial treatment

Patients will receive treatment within the institution’s distal radius fracture clinic. They will undergo a clinical and radiographic examination, with bilateral x-rays of the wrists in posteroanterior (PA) and lateral (L) views. After applying inclusion and exclusion criteria, eligible individuals will be informed regarding the nature and objective of the study, by reading the “Informed Consent Form” and will then be enrolled after signing the form. On a pre-scheduled date, the study participant will be anesthetized and undergo a trial, closed reduction of the facture. After the trial fracture reduction, radioscopy will be performed to evaluate reducibility criteria. Patients that have fractures capable of closed reduction will be randomized and treated surgically by one of the two methods of the study. Patients that do not have distal radius fractures capable of closed reduction will be excluded from the study and will receive appropriate treatment.

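### Numeric secondary outcomes go to an unadjusted t-test, although the opposite wrist, already filmed at entry and used as the radiographic reference, could serve as a covariate at no cost

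*Protocol article*

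**What the plan says.** All references are to the protocol article.

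- **Statistical methods.** For between-group comparison of numeric data, a Student's t "test will be used for comparing groups of numeric variables". This is the only between-group method named for such data. No covariate, side-to-side difference or percentage of the opposite side is mentioned. The paired and Wilcoxon tests listed there concern change over time.
- **Secondary outcomes.** Five radiographic parameters, arcs of motion, "palm grip strength" and pinch strength are measured at each visit. The section does not say whether the uninjured side is measured, or whether values are expressed relative to it.
- **Reducibility criteria.** The same five radiographic parameters decide displacement and reducibility, and here the "contralateral side will be used as a reference".
- **Exclusion criteria.** "Patients with bilateral fracture" are excluded, as are those with a prior "degenerative or traumatic disorder of the affected or the contralateral wrist joint".
- **Initial treatment.** At the first examination every patient has "bilateral x-rays of the wrists in posteroanterior (PA) and lateral (L) views".

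**The concern.** The normal values of several of these outcomes differ between people. Ulnar variance and radial length depend on the individual's anatomy, and strength depends on sex, age and build. An unadjusted comparison of two groups leaves that variation in the error term. The patient's other wrist is a natural measure of it, and the protocol already treats it so when it judges displacement and reduction. The outcome analysis, as stated, makes no further use of it.

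Precision is at stake, not validity. The Background anticipates better radiographic parameters with the plate, and goniometry and dynamometry make up the objective functional evaluation. The sample size is derived from DASH alone, so none of these outcomes has a power basis of its own. The randomization section describes no stratification, so a chance imbalance between arms in anatomy or sex would not be corrected by the t-test.

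**Working it through.** **Inputs from the article.** 36 patients per group, 1:1 allocation, 80% power, alpha 0.05. Sidedness is not stated; two-sided is assumed.

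**Input not in the article.** r, the correlation between the injured-side outcome and the contralateral value. It is an assumption, shown over the range 0.3 to 0.8.

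**Step 1: the plan's own figure.** The 36 per group rests on a 10-point DASH difference with no SD, so it cannot be reproduced. Solved backwards with z-values 1.960 + 0.842 = 2.802, it implies SD = 10/2.802 × √(36/2) = 15.1 if nothing is set aside for dropout. If the unexplained 20% allowance means dropout, the implied SD is about 13.5 (36 × 0.8 = 28.8 analysed) or 13.8 (36/1.2 = 30 analysed). This does not bear on the point, which concerns secondary outcomes. Only n = 36 is carried forward.

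**Step 2: the stated method.** The difference detectable by a t-test at 36 per arm (normal approximation) is 2.802 × √(2/36) = 2.802 × 0.2357 = 0.66 SD.

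**Step 3: adjusting for the contralateral value.** In a linear model with treatment and the contralateral value, residual variance is multiplied by 1 − r². The detectable difference becomes 0.66 × √(1 − r²) SD, and 36 per arm is worth 36/(1 − r²) per arm analysed without adjustment.

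**Step 4: the alternative of a t-test on the side-to-side difference.** With equal SDs on both sides (assumed), variance is multiplied by 2(1 − r).

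| r (assumed) | 1 − r² | Variance removed | Equivalent n per arm | Detectable, adjusted (SD) | 2(1 − r) | Detectable, simple difference (SD) |
|---|---|---|---|---|---|---|
| 0.3 | 0.91 | 9% | 39.6 | 0.63 | 1.40 | 0.78 |
| 0.5 | 0.75 | 25% | 48.0 | 0.57 | 1.00 | 0.66 |
| 0.7 | 0.51 | 49% | 70.6 | 0.47 | 0.60 | 0.51 |
| 0.8 | 0.36 | 64% | 100.0 | 0.40 | 0.40 | 0.42 |

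For a true difference of 0.66 SD, power rises from 80% to 84%, 90%, 97.5% or 99.7% with adjustment. With the simple difference it is 66%, 80%, 95% or 99%.

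**Step 5: comparing the two uses of the opposite side.** Since 1 − r² = (1 − r)(1 + r) and 1 + r is at most 2, the adjusted model never has a larger variance factor than the simple difference. The simple difference is worse than no adjustment when r is below 0.5. The adjusted model costs one residual degree of freedom (72 − 2 = 70 becomes 69), which is immaterial.

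**The case against.** The strongest reply is that a reader might infer that raw injured-side values are compared, and the article does not say so. It names a test and leaves the form of the variable open. A t-test can be applied to a percentage of, or a difference from, the opposite side. For the radiographs the same five parameters appear under Reducibility criteria as losses or differences against the other wrist, so the outcomes may be meant on that scale. A condensed article may also leave variable definitions to the full protocol or analysis plan. This stands, and the point does not assert a raw comparison. It does not remove the point, because the stated test is unadjusted on either scale, and Step 5 shows that a t-test on side-to-side differences is never more efficient than the adjusted model.

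Other objections also stand and limit the point:

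- A reader might take the design to guarantee a healthy opposite limb. It does not. The exclusions cover bilateral fracture and prior disorder of the wrist joint; they do not expressly cover the fingers and thumb, which determine pinch and metacarpophalangeal motion.
- The gain depends on an unknown correlation. At r = 0.3 the detectable difference moves only from 0.66 to 0.63 SD, and r need not be the same for every outcome and visit. Early strength and motion, with a fixator or splint in place or only recently removed, may depend little on the opposite side.
- In a healthy wrist articular fragment displacement should be near zero and vary little, so it can explain almost nothing.
- Contralateral grip, pinch and motion are not documented as collected. Dominance is absent from the listed baseline items, but an article may shorten such a list, so its absence is no finding.

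**Conclusion.** The point holds as an inexpensive improvement to the analysis, not as an error. The article fixes an unadjusted t-test for numeric outcomes and does not carry the contralateral wrist into the outcome analysis, although its radiographs exist and it is already the reference for these radiographic parameters.

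The benefit ranges from slight (9% less variance at r = 0.3) to substantial (64% less at r = 0.8). It rests on the assumed r and on a two-sided 5% test with all 36 per arm analysed. A reader might conclude that the trial is certainly much less precise than it need be. The documents give no correlation, so they support only that precision may be lost.

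Nor do they support any claim of bias: under randomization the unadjusted comparison is valid. DASH and pain, the primary outcomes, are untouched.

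**What to change.** **Free.** Analyse ulnar variance, volar tilt, radial inclination and radial length with a linear model containing treatment and the patient's contralateral value from the entry films. Use this in place of a t-test, whether on the values themselves or on side-to-side differences. The films are already taken, so the change is one line in the analysis plan plus recording the contralateral readings. State the scale on which each parameter is analysed. Articular fragment displacement can stay as it is.

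**Optional, at small cost.** For grip, pinch and motion, measure the uninjured side once with the same device at an existing visit and record whether the injured hand is dominant. Then use the same model, with dominance added. This takes a few minutes per patient and one extra data item. If these measurements are already made under the full protocol, only the analysis wording needs to change.
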